#### Power and Missing Data

The analyses in this aim take an exploratory approach to establishing phenotypes with latent variable mixture models and isolating common trajectories based on Bayesian networks. As such, we do not have a targeted hypothesis with which to power this analysis for minimum detectable effect sizes but rather a model selection approach using the Bayesian information criterion. With 500 participants, we expect that our sample size will be well above the number of nodes in the Bayesian network, which will allow for an accurate estimation of the conditional probabilities in the network [54,55].

We will assess the risk of bias owing to missing data by looking at patterns of missing measurements at each phase of the patients’ trajectories, although we expect most missingness to be postdischarge. Reasons for missing measurements will be tabulated with a focus on differentiating missed measurements for logistical reasons from dropouts or intermittent missingness potentially related to the condition of the patient. If >10% (25/250) of the patients have missing outcome measurements for any of the follow-up measures or if the comparisons of baseline characteristics between patients with missing and nonmissing measurements indicate considerable imbalances, rather than only looking at complete cases, we will apply the structural expectation-maximization algorithm, an imputation method that directly processes data with missing values while fitting the Bayesian network [56]. This method incorporates baseline and follow-up factors beyond the variable being analyzed to account for the dependence of missing data on other factors. TBI history is a primary piece of data required for admission to the program. It is unlikely that any data will be missing for TBI history. However, if >20% (>50/250) of the sample has missing data related to TBI history, the study should be stopped.

### Aim 3

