#### Data Analysis

After calculating descriptive statistics (proportions and quantiles for discrete variables and means and SDs for continuous variables) of VHA and DoD intake measures before IETP admission, we will fit a latent variable mixture model, a multivariate statistical technique used to classify individuals into interpretable categories based on a set of measurements (described in the *Measures and Data Collection Procedures* section) [36,42-49]. Similar to cluster analyses, the latent variable mixture model is an exploratory technique to identify underlying constructs associated with multiple variables, in our case, the underlying comorbidity phenotypes. On the basis of prior work, we expect 2 to 3 groups each with n=approximately 100-200 participants [36]. Health system data identifying the treatment provided are not likely to have missing data owing to the professional responsibility to document. Each visit requires a primary diagnosis for care, which will lead to data available at each visit; therefore, we expect little to no missing data.

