#### Identify Components of IETP Associated With Sustainment and Improvement Trajectories

Outcomes currently identified by operational and clinical stakeholders that are collected at all sites (Tables 3 and 4) will be included in the survey to develop longitudinal outcome trajectories. On the basis of stakeholder feedback, we will also measure and describe community reintegration, employment, retention in the military where relevant, compliance to discharge from the TBI care plan, reasons for difficulty in care plan compliance, and unmet rehabilitation needs. Per operational partners’ request, we will also use VHA and DoD data to identify use relevant to discharge (eg, TBI care plan within primary, mental health, specialty care, or emergency care).

We will use Bayesian network analysis to generate a directed acyclic graph, which probabilistically describes the trajectory of symptoms, care, and outcomes for IETP participants. This network will enable us to explore the contribution of the baseline phenotype to the decision to use a particular treatment course and the contribution of those treatments to the participants’ resulting outcome measures [53]. Using a hill-climbing algorithm scored with the Bayesian information criterion, we will establish directional connections between nodes, called edges, and evaluate the robustness of the edges using bootstrapped samples of the data. We will a priori exclude any implausible directed edges (eg, IETP care cannot lead to precare symptoms). The resulting directed network will have edges between the levels: (1) phenotypes, (2) treatment, and (3) outcomes, while disallowing connections that go from levels 2 to 1 or 3 to 2 or 1. We can allow edges between nodes within the treatment level of the network to better understand the interactions between treatments and to assess how the treatments individually and in combination probabilistically affect patient outcomes. By fitting this model, we can isolate the most probable trajectories between TBI phenotypes and treatments and then determine which treatments have a higher probability of positive long-term outcomes. To gain an understanding of the treatment courses on outcomes, we will present a graphical display of the nodes and edges, the conditional probabilities calculated between nodes that estimate the probability of long-term outcomes given the participants’ IETP components and comorbidity phenotypes, and the robustness measures from bootstrapping.

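### Having more participants than network nodes does not show that the conditional probabilities will be accurate, and a component edge dropped by BIC is not evidence that the component is ineffective

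*Protocol article*

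**What the plan says.** Under Aim 2, Power and Missing Data, the protocol calls the analysis exploratory and states that "we do not have a targeted hypothesis with which to power this analysis for minimum detectable effect sizes". It then offers one argument that the sample is adequate: with 500 participants, the "sample size will be well above the number of nodes in the Bayesian network, which will allow for an accurate estimation of the conditional probabilities". Two references are cited for this. The article gives no node count, no number of states or parents per node and no target width.

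The probabilities concerned are described under Identify Components of IETP Associated With Sustainment and Improvement Trajectories. They are to "estimate the probability of long-term outcomes given the participants’ IETP components and comorbidity phenotypes". Edges among treatments are allowed, partly "to assess how the treatments individually and in combination probabilistically affect patient outcomes". The structure comes from a hill-climb with BIC as the score, and bootstrap samples are used to judge how robust the edges are.

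On phenotypes, the Data Analysis section of Aim 2 says "we expect 2 to 3 groups each with n=approximately 100-200 participants". Measures and Data Collection Procedures gives about 500 as the population to be surveyed. Power and Missing Data expects most missing data after discharge and uses 250 as the denominator for its missing-data thresholds.

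**The concern.** The node count is the wrong yardstick. A discrete outcome node needs one probability for each combination of its parents' values. Those combinations multiply as parents are added, while the node count can stay the same. The same 500 patients and the same nodes can therefore give tight or very wide estimates, depending on the structure that is learned.

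The 500 is also a survey population, not a count of patients with long-term outcomes. The outcome nodes are where the protocol itself expects data to be missing.

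The sections on the preimplementation stage, Aim 3 and the conclusions say that Aim 1 and Aim 2 findings will support implementing effective components and deimplementing ineffective ones. If the network's probabilities are described as accurate, sites may give them more weight than they can bear. Sites may also read a component with no edge to outcome as one that does not work.

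**Working it through.** **No figure to reproduce.** The protocol states no formula, node count or width, so the check is whether its conclusion follows from its premise.

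**Inputs from the protocol:** N = 500; 250 as the alternative denominator; 2 to 3 phenotypes; the outcome conditioned on phenotype and components.

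**Assumptions:** a binary outcome, binary components, equal cells, and p = 0.5 (the widest case).

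**Step 1, precision by number of parents.**
Combinations = phenotypes × 2^k for k components. Patients per combination m = N / combinations. 95% half-width = 1.96 × √(0.25/m).

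Example with 3 phenotypes, k = 2 and N = 500: 3 × 4 = 12 combinations, m = 500/12 = 41.7, half-width = 1.96 × √(0.25/41.7) = 15.2 points.

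| Parents (3 phenotypes) | Combinations | N=500: m, half-width | N=250: m, half-width |
|---|---|---|---|
| phenotype only | 3 | 166.7, ±7.6 | 83.3, ±10.7 |
| + 1 component | 6 | 83.3, ±10.7 | 41.7, ±15.2 |
| + 2 components | 12 | 41.7, ±15.2 | 20.8, ±21.5 |
| + 3 components | 24 | 20.8, ±21.5 | 10.4, ±30.4 |

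With 2 phenotypes and N=500 the half-widths are ±8.8, ±12.4 and ±17.5 for one, two and three components. Wilson intervals are slightly narrower (for example 19.7 instead of 21.5).

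A half-width of ±10 points needs 0.25 × (1.96/0.10)² = 96.04, so 97 patients per combination. That allows 500/97 = 5 combinations, or 250/97 = 2. Three phenotypes by one component is already 6.

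**Step 2, what BIC does.**
Adding a k-th binary component when a 3-class phenotype is already a parent adds 3 × 2^(k−1) parameters, at a cost of ln(N)/2 each. I found the risk difference d, centred on 0.5 with an even split, at which the expected log-likelihood gain N × [ln 2 + (0.5+d/2) ln(0.5+d/2) + (0.5−d/2) ln(0.5−d/2)] equals that cost.

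- N=500, first component: cost 3 × 6.215/2 = 9.3, so d ≈ 19 points.
- N=500, second: cost 18.6, so d ≈ 27 points.
- N=500, third: cost 37.3, so d ≈ 38 points.
- N=250, first and second: about 26 and 36 points.

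If phenotype is not a parent, the first component adds one parameter (cost 6.215/2 = 3.1) and d ≈ 11 points, so the 19 and 27 depend on phenotype being in the parent set.

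**Step 3, simulation of BIC parent selection for one outcome.**
Assumptions: three phenotypes 10 points apart; six components, three with true additive effects of 10 to 25 points; uptake 50% or 80%; N = 500 or 250.

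- The 24-combination table was selected in 0 of 16,000 runs, and tables of 12 or more combinations in at most 0.5% of runs.
- In a repeat with 400 runs per setting at N=500, the average number of the three real effects kept was 0.3 to 0.6 when each was 10 points, 0.8 to 1.3 at 15, 1.5 to 2.0 at 20 and 2.0 to 2.8 at 25.
- About 26% to 52% of patients had a fitted probability more than 10 points from the true value given their phenotype and components. The repeat gave 28% to 48% at N=500 and 38% to 57% at N=250.

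**The case against.** The strongest reply is that the plan does not cross-tabulate outcomes against every component. Parents are chosen by BIC, which penalises large tables, and Step 3 confirms that 24-combination tables are essentially never selected. The phrase about treatments in combination explains why edges within the treatment level are allowed; it does not promise a full table. This stands.

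A reader might therefore infer too much: that the sites will be handed probabilities resting on a handful of patients, or that cells for patients who received none of several components will be nearly empty. The documents do not support that. They give no uptake figures. Calling the program bundled does not mean that most patients receive most components, and the treatment section expects care to differ with clinical presentation.

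The pruning does not rescue the accuracy claim, however. It exchanges wide intervals for omitted effects, and Step 3 shows that the fitted probabilities are then often well away from the true ones.

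Other replies stand in part:
- An exploratory analysis needs no power calculation. That is right, and none is asked for; the fault is the positive statement of accuracy.
- Structural expectation-maximization lets incomplete records contribute, but it does not restore the information lost when a survey outcome is unobserved.
- The two cited references could not be consulted. They may support a narrower statement.
- Interval methods and reporting rules may sit in a fuller plan, so their absence from an article is not itself the fault. In this text the bootstrap is described for edges, which says nothing about the width of a conditional probability.

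**Conclusion.** The point holds as follows: the stated argument does not support accurate estimation of the conditional probabilities. To say that accuracy will certainly not be reached would go too far, because the learned structure is unknown. With phenotype and one component at N=500, precision is moderate (±9 to ±11 points for two or three phenotypes). With two components it is ±12 to ±15, and at 250 it is ±17.5 to ±21.5.

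The second consequence is that BIC can omit component effects of moderate size, so a missing edge is not evidence of no effect. The protocol does not say that it will read missing edges in that way. It also gives no other rule, in this article, for calling a component ineffective.

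The sizes rest on binary coding, equal cells, p near 0.5 and, for the 19- and 27-point thresholds, a three-class phenotype already among the parents. Unequal uptake would widen some cells and narrow others. The point should be fixed, but it does not undermine the evaluation: Aim 2 is declared exploratory, and the lack of a comparison group is acknowledged.

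**What to change.** 1. Replace the sentence comparing 500 with the node count by a precision statement: the expected number of survey responders with outcomes, the planned states per node, the plausible parent combinations, and the resulting half-widths. State whether 500 or 250 is the working denominator.
2. Report an interval for every conditional probability, from a bootstrap that repeats the whole pipeline: mixture model, structure search and probability estimation.
3. State that the absence of an edge will not by itself be read as evidence that a component is ineffective.

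A cap on parents per outcome and a minimum cell size for reporting are optional, since BIC already does much of that work.

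The cost is some wording, extra computing for the full bootstrap, and a stated precision that looks less favourable than the present one.

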#### Measures and Data Collection Procedures

Data from each IETP participant will be obtained from site leads beginning with Tampa (2015 to present; n=approximately 350). We will obtain identifiers that allow linkage to VA and DoD health system data and create a study crosswalk database behind the VA firewall that includes the encrypted identifier, a study ID, and contact information for interview and survey administration. We will obtain intake and discharge measures from each IETP site. We will assess IETP fidelity based on the IETP characterization table (Multimedia Appendix 1) using a checklist (Multimedia Appendix 2) and chart abstraction focusing on the admission note, admission IETP care plan, discharge TBI care plan, and discharge summary, which are highly accurate in describing the reasons for seeking treatment, baseline status, the type of treatment recommended, the type of treatment received, and outcomes on discharge (Multimedia Appendix 12).

We will also link these IETP data to VA and DoD health system data, as we have done previously [36], to obtain information on physical and mental health, medications, and military demographic data before and after IETP. As approximately 90% (225/250) of participants in the IETP are active duty at the time of treatment with the goal of returning to full duty and operational partner priority outcomes include return to duty or employment, the use of VHA data (eg, Patient Health Questionnaire-9 [PHQ-9] and PTSD checklist-5) is not a feasible approach to long-term outcomes. Therefore, we will conduct a survey using a VA-approved web-based survey software for participants of IETP (2015-2022; approximately 500) using a Modified Dillman Method, which we used in prior VA studies (Multimedia Appendix 13) [37-40]. We will begin a survey of earlier IETP graduates in the first year of the study and send surveys to new graduates 6-9 months post study completion. The final outcome measures included in the survey will be developed in collaboration with stakeholders. The current list of stakeholder-identified measures that are evaluated at intake and discharge include the PHQ-9, PTSD checklist-5, MPAI, and the Neurobehavioral Symptom Inventory.

We will also use VA and DoD health system data to describe health system outcomes such as use, new diagnoses, and adverse outcomes, which will, together with data baseline, discharge, fidelity, and discharge outcomes, be used to develop trajectories of recovery.

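### The missing-data check compares groups on baseline characteristics only, although most missingness is expected after discharge and discharge and linked post-IETP data could be used

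*Protocol article*

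**What the plan says.** All of this is in the Protocol article, Methods, Aim 2.

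**Power and Missing Data** sets out four elements:
- It examines "patterns of missing measurements at each phase" of the patient trajectory, with the remark "although we expect most missingness to be postdischarge".
- It tabulates reasons for missing measurements, with a focus on "differentiating missed measurements for logistical reasons from dropouts or intermittent missingness potentially related to the condition of the patient".
- It leaves complete-case analysis for the structural expectation-maximization (EM) algorithm under either of two conditions. The first is "If >10% (25/250) of the patients have missing outcome measurements for any of the follow-up measures". The second is that "comparisons of baseline characteristics between patients with missing and nonmissing measurements indicate considerable imbalances".
- It says of structural EM: "This method incorporates baseline and follow-up factors beyond the variable being analyzed to account for the dependence of missing data on other factors".

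**Measures and Data Collection Procedures** states that "approximately 90% (225/250) of participants in the IETP are active duty at the time of treatment with the goal of returning to full duty" and lists return to duty or employment among the operational partner's priority outcomes. Long-term outcomes come from a web survey. The same section links participants to VA and DoD data "to obtain information on physical and mental health, medications, and military demographic data before and after IETP".

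**Tables 3 and 4** place the Mayo-Portland Adaptability Inventory (MPAI), PHQ-9, PTSD checklist-5 and Neurobehavioral Symptom Inventory at baseline, discharge and survey. They place diagnoses, health care use, and medications and procedures after IETP as well as before. Treatment received is abstracted from charts. None of the discharge, chart or health-system data depends on answering the survey.

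**The concern.** A comparison of respondents and non-respondents detects selective loss only through the variables compared. Here the loss is expected at the survey, months or years after discharge, while the named comparison uses information from before treatment. Non-response that follows from the patient's state at discharge, or from what happened afterwards, reaches a baseline comparison only in diluted form.

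In this cohort such a link is plausible. Most patients aim to return to full duty, and return to duty is a priority outcome. Whether someone is serving, away or separated when the survey arrives may affect both the chance of a reply and the scores that a reply would contain. The split between logistical and condition-related reasons has no clear place for that case.

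At stake is the credibility of the risk-of-bias statement on the long-term survey outcomes. Those outcomes enter the Bayesian network, and the findings are meant to inform which components are implemented or deimplemented.

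**Working it through.** **Stated figures.** 225/250 = 90% and 25/250 = 10% reproduce. I read the trigger as 10% of patients. (The base of 250 sits beside a stated 500 participants in the same section, and 25/500 would be 5%. That is a separate matter.) No survey response rate is given, so every rate below is an assumption.

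**1. Dilution at baseline.** Assume correlations of 0.5 (intake with discharge), 0.6 (discharge with survey) and 0.4 (intake with survey). Assume 50% response, with log-odds of response changing by 0.4 per SD of discharge score. In a simulation of 2,000,000 patients:
- respondents and non-respondents differ by 0.384 SD at discharge;
- at baseline they differ by 0.5 × 0.384 = 0.192 SD;
- with half responding, respondents lie 0.384/2 = 0.192 SD from the full-cohort discharge mean, so their survey mean is off by 0.6 × 0.192 = 0.115 SD (simulated 0.116).

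The baseline comparison shows half of the imbalance that the discharge scores would show.

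**2. Response depending on later duty status.** Let p be the true share returned to duty, and r1 and r0 the response rates on and off duty. The share observed among respondents is p·r1 / [p·r1 + (1 − p)·r0]. With p = 0.6, r1 = 0.4 and r0 = 0.6 this is 0.24/(0.24 + 0.24) = 0.50, which is 10 points too low. For p from 0.5 to 0.8:

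| Response on / off duty | Error in observed return to duty |
|---|---|
| 30% / 60% | 13 to 17 points too low |
| 40% / 60% | 7 to 10 points too low |
| 50% / 60% | 3 to 5 points too low |
| 50% / 50% | 0 |
| 60% / 40% | 6 to 10 points too high |

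**3. Would the baseline comparison show it?** I used 2000 simulated cohorts of 500, about 60% on duty, with response 40% on and 60% off duty. The outcome was 0.5 units better on duty, with a baseline slope of 0.5 and residual SD 0.8. The log-odds of being on duty fell by 0, 0.3 or 0.6 per SD of baseline severity.

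| Dependence of duty on baseline | Runs with baseline difference < 0.2 SD | Complete-case bias | Bias after adjusting for baseline | Bias after adding duty status |
|---|---|---|---|---|
| 0 | 97% | 0.050 | 0.050 | 0.000 |
| 0.3 | 95% | 0.065 | 0.050 | 0.001 |
| 0.6 | 86% | 0.078 | 0.047 | 0.000 |

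**4. Where complete-case analysis survives.** About 52% are missing in step 3, so the 10% condition is met whatever the baseline balance. Complete cases are kept only with 10% or less missing and a balanced baseline. With 88%/96% response and p = 0.6, the respondent share is 0.528/(0.528 + 0.384) = 0.579, or 2 points too low with 8.8% missing. At exactly 10% missing the extremes for p = 0.6 are (0.60 − 0.10)/0.90 = 0.556 if every non-respondent had returned, and 0.60/0.90 = 0.667 if none had. The error is thus at most 4 points down or 7 points up.

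**The case against.** The strongest reply is that the plan does more than compare baselines. It looks at missingness at each phase. Its two conditions are joined by *or*, so at any realistic level of survey non-response structural EM replaces complete cases regardless of baseline balance. That method is said to use follow-up factors as well as baseline ones. If response depends only on the discharge score, as in step 1, conditioning on intake and discharge brings the bias to about 0.00; cutting the discharge score into three categories leaves 0.02. Most of this stands. The complete-case biases above would mostly not be relied on.

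A reader might also infer that absence on duty will be filed as logistical and dismissed, so that a distorted sample is passed as sound. The documents do not support that. They do not define logistical, do not say where duty absence belongs, and attach no decision to the tabulated reasons. The condition-related category could be read to include it.

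It is fair to add that the aim is exploratory, that an article may leave variable lists to a fuller plan, and that the linked data are not shown to contain duty status at the survey date.

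Two things survive. Patterns by phase show when values are missing, but the only stated comparison of who is missing uses baseline. And structural EM, as usually applied, relies on data being missing at random given the variables in the model; post-discharge duty status is not named among them. In step 3, leaving it out kept a bias of about 0.05 units.

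**Conclusion.** The point holds as a cheap improvement, not as an error that invalidates the analysis. The stated comparison is weak for the missingness the plan expects, and it can understate selective non-response in the risk-of-bias assessment and in the imbalance condition. Its effect on the choice of complete cases is limited to 10% or less missing, where the illustrative distortion in return to duty is about 2 points. Above 10%, what remains is a possible residual bias of about 0.05 outcome units under the assumed scenario, if duty status affects response and is left out of the imputation.

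These sizes rest on assumed response rates, correlations and outcome differences. The true size and direction are unknown: equal response by duty status gives no bias from this source, and better response among those on duty reverses the sign.

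**What to change.** In Power and Missing Data:
1. Compare survey respondents and non-respondents not only on baseline characteristics but also on discharge MPAI, PHQ-9, PTSD checklist-5 and Neurobehavioral Symptom Inventory scores, components received, linked post-IETP diagnoses and use, and duty or separation status where the linked data contain it.
2. Use this wider comparison for the imbalance condition and for the risk-of-bias statement.
3. Name the same variables among the structural EM factors.
4. Tabulate duty-related non-response as its own, potentially outcome-related category, separate from administrative failures such as an unsent survey or an invalid address.

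The cost is one extra table from data mostly already planned, a few more model variables, and a check of whether duty status can be obtained through the DoD linkage. The stated risk of bias may become less favourable.

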**Pre-PEI**			
	Identify and align needs and goals	Work with a team that understands needs and goals from the TBI^a^ and implementation perspective	Ongoing communication and meetings to understand needs and identify priorities
	Engage stakeholders	Prior push to implement not successful	Site representatives recruited to facilitate a bottom-up pull and buy-in from local staff. Input on study design and findings were sought from a stakeholder panel including veterans, service members, VA^b^ and DoD^c^ administrators, and clinicians
	Develop measures and data	Program evaluation data are not standardized and readily accessible	Site representatives recruited to facilitate engagement of stakeholders for data collection. Meetings with PM&R^d^ partners and various stakeholders to identify and prioritize outcomes

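### Aim 2 defaults to a complete-case network and switches to structural EM on a trigger that omits intake and TBI-history data and is not tied to joint completeness

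*Protocol article*

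**What the plan says.** The rule is in the protocol article, Aim 2, Power and Missing Data. Complete cases are the default, and two triggers joined by an or lead away from it:

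- a numeric one: "If >10% (25/250) of the patients have missing outcome measurements for any of the follow-up measures";
- a qualitative one: "or if the comparisons of baseline characteristics between patients with missing and nonmissing measurements indicate considerable imbalances".

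If either fires, the network is fitted with structural EM ("rather than only looking at complete cases, we will apply the structural expectation-maximization algorithm"). The same section plans a descriptive review, "looking at patterns of missing measurements at each phase" of the patient's trajectory, tabulates reasons for missingness, and expects most of it after discharge.

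TBI history has its own rule. It is needed for admission, so almost none is expected to be missing, but "if >20% (>50/250) of the sample has missing data related to TBI history, the study should be stopped".

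Three other places bear on the rule. Characterize IETP Participants builds the phenotypes partly from TBI history and from symptom inventories given at admission. Identify Components of IETP Associated With Sustainment and Improvement Trajectories links phenotypes, treatments and outcomes in one network. Table 3 lists four instruments, each taken at baseline, at discharge and in the survey.

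**The concern.** A complete-case network needs every variable in it to be present for the same patient. The numeric trigger looks at one part of that requirement, the follow-up outcomes. Missing intake inventories cannot set it off. Nor can TBI history missing in up to 20%: the only stated consequence comes above that level, and it is stopping, not imputation. Both are inputs to the phenotype level.

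The trigger can also be read in two ways. It may count patients who miss at least one follow-up measure, or it may be checked measure by measure. On the second reading every measure can pass while the share of patients incomplete on at least one is well above 10%.

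The qualitative trigger has no threshold and compares baseline characteristics only, so it cannot reveal non-response driven by status after discharge. That matters here. Measures and Data Collection Procedures says about 90% of participants are on active duty with the aim of returning to full duty, and that "operational partner priority outcomes include return to duty or employment".

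The network is meant to show which treatments go with a higher probability of good long-term outcomes, and the findings inform deimplementation of ineffective components (Preimplementation Stage; Aim 3 Overview; Conclusions). Selective loss of patients could distort those conditional probabilities while the stated rule reports no problem.

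**Working it through.** **1. The plan's own figures.** 25/250 = 10% and 50/250 = 20%, so the thresholds reproduce on a base of 250. The same section gives 500 participants. On that base the same counts are 25/500 = 5% and 50/500 = 10%. No power figure needs checking, because the article says this aim is not powered.

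**2. Inputs.** m = 10% missing per measure (the trigger's limit); k = 4 survey measures (Table 3); N = 500. How missingness overlaps between measures is not in the documents. It is an assumption here, and is ranged.

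**3. Patients lost under the per-measure reading, every measure exactly at the limit so that the numeric trigger stays silent.**

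- Nested (the same patients miss all four): loss = m = 10%.
- Independent: 1 − (1 − m)^k = 1 − 0.9^4 = 34.4%.
- Disjoint: k × m = 4 × 0.10 = 40%.
- In between: equicorrelated latent normals, a measure being missing when its latent value lies below the 10th percentile (simulation, 1,000,000 draws).

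| Overlap | Patients lost, k = 4 | Complete of 500 |
|---|---|---|
| Nested | 10.0% | 450 |
| Latent correlation 0.9 | 16.3% | about 419 |
| Latent correlation 0.7 | 21.7% | about 391 |
| Latent correlation 0.5 | 25.8% | about 371 |
| Independent | 34.4% | about 328 |
| Disjoint | 40.0% | 300 |

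A second description of a survey gives a similar size. Take 8% unit non-response and item non-response of 1 − 0.90/0.92 = 2.2%, so that each measure is again 10% missing. The loss is 1 − 0.92 × 0.978^4 = 15.7%.

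**4. Per-patient reading.** If the 10% counts patients missing at least one follow-up measure, follow-up loss under complete cases cannot exceed 10%.

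**5. If discharge measures count as follow-up too (k = 8).** The losses are 10.0% (nested), 19.5% to 36.6% (latent correlation 0.9 to 0.5), 57.0% (independent) and 80.0% (disjoint). This needs 10% missing at discharge as well, and the article expects most missingness later.

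**6. Adding TBI history at its tolerated 20%, independent of follow-up.** With nested follow-up the loss is 1 − 0.9 × 0.8 = 28%. With four independent measures it is 1 − 0.9^4 × 0.8 = 47.5%, leaving about 262 of 500. Both figures assume that a patient without TBI history drops out of the network, which the article does not state.

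**7. Effect of the base.** If the limit is really 25 of 500, or 5%, four measures lose 5% (nested), 18.5% (independent) or 20% (disjoint). The base therefore changes the result materially.

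**The case against.** Much of the opposing case stands.

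- **The trigger will often fire.** The survey reaches back to 2015 graduates, and Potential Limitations names poor survey participation as a pitfall. Non-response above 10% is likely, and structural EM would then be used. This limits the practical harm. It also means the trigger protects little and mainly leaves an ambiguous, data-dependent choice of method.
- **One survey supplies all four long-term measures.** Non-responders will mostly miss all of them together. A reader might infer from the independent case that a third or more of patients would be discarded. The documents do not support that as the expected loss: it needs the per-measure reading, every measure at its limit, and independent or disjoint missingness.
- **The 10% rule is not the only route, and TBI history is not ignored.** The imbalance trigger can fire at any level of missingness, and TBI history is counted against 20% with stopping as the consequence. The gap is narrower: TBI history below that level neither contributes to the switch nor has any stated handling.
- **Linked data.** A reader might infer that structural EM would ignore the linked VA and DoD data. Power and Missing Data says the method draws on baseline and follow-up factors. Table 4 lists post-IETP diagnoses, use and medications as trajectory measures, and Identify Treatment Received During IETP merges the linked data for the outcome analyses. What remains is to confirm that these variables are nodes.
- **Table 1.** Its remark, "Program evaluation data are not standardized and readily accessible", is a challenge named before the evaluation and paired with a solution. It does not show that intake scores or TBI history will be missing. Equally, the expectation of almost no missing data in the Aim 2 Data Analysis section is argued from visit documentation and diagnoses, not from inventories.
- **Exploratory aim, detail left to a fuller plan.** That would answer a complaint about something omitted. Here the article states a rule, and the rule itself is the difficulty. The planned review of patterns and reasons at each phase helps interpretation, but the article attaches no change of method to it.

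**Conclusion.** The concern holds in a limited form. The article makes complete cases the default, with a numeric switch that leaves out intake inventories and TBI history missing in up to 20%, and a second switch that has no threshold and looks at baseline only.

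The size depends on how the rule is read. Per patient, follow-up loss is at most 10%. Per measure, with four survey measures each at the limit, it is 10% if nested and about 16% to 26% at latent correlations of 0.9 to 0.5. It reaches 34% to 40% only under independence to disjointness, which is unlikely with a single survey. The correlations are assumptions; the documents give no figure for them.

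Because the switch would often be triggered by survey non-response, this is a modest but worthwhile correction to a stated rule, not a flaw that undermines the aim.

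**What to change.** Make structural EM the primary fit in all cases, including for missing intake inventories and TBI-history inputs, and report the complete-case network as a sensitivity analysis. This removes the data-dependent choice of method and says what happens to TBI history that is missing but below the stop threshold.

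If a trigger is preferred, define it as the share of patients incomplete on any network variable (intake, TBI history, discharge, survey).

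In either case:

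- confirm that the post-IETP VA and DoD variables in Table 4 enter the network, so that information available whether or not a patient answers the survey can inform the missing outcomes;
- reconcile the base of 250 in the thresholds with the 500 participants in the same section.

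Structural EM, bootstrapping and linkage are already planned. The cost is a change of wording and some extra computing time.
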